### Intervention content and delivery

2.6

#### ‘NeedCraft’ and ‘NeedNurture’

2.6.1

The current study involves two interventions designed to enhance need satisfaction in the workplace. NC is designed to teach employees how to craft their work experiences to better meet their psychological needs. In parallel, NN targets managers, aiming to upskill them to support their subordinates’ basic psychological needs. This standardized protocol will guide the design, effective implementation, and evaluation of the interventions and will also aid stakeholders and managers in future action orientation through more effective decision-making about employee well-being, policy design, etc., (De Angelis et al., 2020).

Both interventions are grounded in Kolb’s learning theory (Kolb, 1984), which holds that effective learning occurs through four stages (see Tables 1, 2). First, learners engage in concrete experiences, followed by reflection on these experiences in the second stage. In the third stage, learners develop abstract ideas about new behaviors and acknowledge their potential benefits. Finally, they actively test these new behaviors, creating new experiences (Demerouti et al., 2021; Kolb et al., 2001; Nielsen and Randall, 2013). NC and NN incorporate these four stages into their learning processes to ensure comprehensive skill development and behavioral change.

The training will be delivered in person, as research shows that face-to-face training tends to yield higher participant satisfaction compared to online formats (Laporte et al., 2024). The program structure consists of an initial 2.5-h training session (see Steps 1–3 in Tables 1, 2), followed by 2 weeks to implement newly acquired skills and behaviors in the workplace. After this implementation phase, a 2-h reflection meeting will be held (see Step 4 in Tables 1, 2) to discuss experiences, reinforce learning, and adjust strategies as needed.

In the NC intervention (see Table 1), employees are guided through complementary activities that help them become more aware of opportunities and resources to satisfy their psychological needs (Laporte et al., 2021). Such activities can include individual employees negotiating opportunities for more independent decision-making with their supervisor (autonomy crafting), reflecting on successes (competence crafting), or initiating a social activity (relatedness crafting) (Kotze et al., 2024). During the 2.5-h intervention training session, participants will be expected to reflect on their own jobs through a job analysis. Such a job analysis speaks to employees’ involvement, proactivity, and improved performance in their jobs (Rudolph et al., 2017) and will help them identify and relate to the need crafting training and its applicability to their daily tasks more easily. Through this, they will be better equipped to identify opportunities to initiate and apply the newly acquired need crafting capabilities in their everyday jobs.

As part of the need crafting training, participants will be introduced to the concept of need crafting, as well as autonomy, competence, and relatedness crafting, and SMART (specific, measurable, achievable, realistic, and time-bound) goal setting. Toward the end of the 2.5-h intervention training session, participants will be required to apply this newly acquired knowledge to compile a personal need crafting plan (employees). Examples of need-specific activities for each stage of the NC training, drawn from the participant workbook, are provided in Table 1.

At the same time, the NN intervention (see Table 2) offers parallel training for managers, equipping them to support their employees’ basic psychological needs. When managers are more need-supportive toward employees, through behaviors such as encouragement, appreciation, and showing understanding, they promote employees’ need-based experiences. However, managerial behaviors such as criticism, rejection, excessive pressure, or simple neglect and ignoring can have the opposite effect on employees’ need-based experiences (Huyghebaert-Zouaghi et al., 2023). Indeed, employees who believe that speaking up may embarrass their supervisors or have negative career consequences are more likely to engage in defensive silence, while perceived power distance is independently associated with such silence (Şahin et al., 2021). These implicit beliefs may persist even when managers appear to encourage employee voice (Detert and Edmondson, 2011). Deliberate managerial training may therefore help managers communicate consistently that employee initiative, including proactive need crafting, is valued and will not be penalized.

Examples of the need-supportive behaviors practiced during each stage of the NN training are provided in Table 2.

This dual-level approach aligns with the IGLO model, which emphasizes targeting multiple organizational levels to maximize intervention impact. Focusing solely on individuals may limit overall impact if other levels, such as leadership or organizational policies, are not addressed simultaneously (Nielsen et al., 2023).

Applying the IGLO model, NC targets the individual level by helping employees enhance their need-based experiences through activities that build personal resources and positive coping mechanisms. Research highlights the positive impact of need crafting interventions at the individual level (Laporte et al., 2024; van den Bogaard et al., 2024). At the leader level, NN focuses on training direct managers to support subordinates’ basic psychological needs. Research also highlights the positive impact of need-support from others. For example, employees who reported their managers as more need-supportive felt better (Huyghebaert-Zouaghi et al., 2023) and more motivated (Van der Vaart et al., 2025). Colleagues constitute an additional source of support: collegial solidarity has been associated with job performance partly through self-efficacy, work engagement, and thriving at work, although a smaller direct association remains (Karataş and Çankır, 2023). This finding is consistent with the pathway targeted in the present protocol, whereby supportive social conditions may foster valued outcomes through employees’ psychological experiences.

Both interventions will rely on goal-setting to strengthen participants’ commitment to crafting their needs. Participants will be required to develop SMART goals as part of their need crafting plans (see Demerouti et al., 2021 for a job crafting intervention). Specific, sufficiently challenging goals can direct attention and effort toward goal-relevant activities and promote persistence, particularly when participants are committed to those goals and receive feedback on their progress (Locke and Latham, 2002). Where appropriate, need-crafting plans will incorporate both personal and organizational objectives, as job crafting interventions that combined these objectives showed moderate effectiveness in improving work engagement (Oprea et al., 2019; Roczniewska et al., 2022).

In conclusion, this intervention protocol focuses on both individuals (i.e., employees) and leaders (i.e., managers), recognizing that employees can occupy different roles (e.g., employee, manager, or colleague). At the individual level, employees (in their role as subordinates) will create a need crafting plan, while leaders (in their role as managers) will develop a need-support plan. This alignment, alongside improved communication and shared standards, is expected to enhance decision-making and contribute to both organizational and individual success (Randall et al., 2009).

The successful transfer and sustainability of training are dependent not only on support outside of the training session, but also on the physical environment in which intervention training takes place (Grossman and Salas, 2011). The trainer’s education and experience contribute significantly to the success of knowledge transfer during intervention training (Nielsen et al., 2023; Vasquez et al., 2026). As a result, the trainer for the interventions will be a qualified and registered organizational psychologist who will provide optimal training support as well as establish conducive and private training environments at the participants’ place of employment. Building on Van der Vaart and Van den Broeck’s (2019) recommendations, the trainer is expected to model need-supportive behaviors throughout the intervention. By experiencing freedom of choice in developing need crafting strategies and understanding the rationale behind the intervention (i.e., autonomy support), participants are more likely to experience autonomy satisfaction. To foster competence support, the trainer will normalize potential challenges that may arise as participants engage in need crafting activities (i.e., inoculation against setbacks) and help them feel competent to address these. Finally, the trainer should actively demonstrate warmth, validation, and genuine support (i.e., relatedness support) so that both managers and employees experience a genuine sense of belonging and acceptance (Slemp et al., 2021).

### Data collection and timeline

2.7

As depicted in Figure 2, all three groups will undergo the same pre-testing simultaneously (before any intervention training commences), and it will comprise the following stages: allocate departments to three groups; perform the pre-test data collection on all three groups at the same time and under the same conditions (T1); provide the first two experimental groups with the intervention supplemented by process and outcome measurements (T2); and provide the delayed experimental group with another baseline measurement of the same pre-test assessment battery to account for any possible changes that may have occurred in the time after they were part of the initial pre-test data collection (T3), as well as commence with post-testing on the first two groups (T3). Thereafter, the third group will receive the intervention (T4), followed by post-testing on all three groups 2 weeks after the training and 1 month after they have completed their intervention training to determine the potential impact on the dependent variable (need satisfaction) within each group as well as measure the possible differences between the groups due to delayed intervention delivery. Each group will undergo two separate post-tests, with all post-testing occurring at four different time points (Demerouti et al., 2021; Laporte et al., 2021).

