### Study design

2.1

The current intervention protocol recommends a quasi-experimental mixed-methods design using a partially randomized delayed-start approach with three experimental groups. Departments (clusters) will be randomized to Group 1 (NC + NN) or Group 3 (delayed NC + NN); departments whose managers do not volunteer will form Group 2 (NC only, non-randomized). Group 2 will demonstrate the superiority of a multilevel intervention (i.e., its cumulative effects), whereas Group 3 will serve as a control group until its members have received the intervention.

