### Allocation to intervention

2.5

All departments that sign up will be treated as separate clusters, followed by randomization (e.g., using a random number generator) to assign each department to either Group 1 (immediate intervention) or Group 3 (delayed intervention). Participants without participating managers will automatically be assigned to Group 2.

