#### Outcome measures

2.8.1

Evaluating the effectiveness of the intervention (i.e., proximal outcomes) will help to determine its success and whether the desired results have been attained. Proximal benefits refer to shorter-term, more immediate, subjective benefits experienced or observed, often as a direct cause of the intervention (i.e., differences in need crafting behavior and perceived managerial support). By contrast, distal outcomes are usually only noticeable over a more extended period of time and often more indirectly as a result of proximal benefits (i.e., changes in need satisfaction).

On the day of training, but before the need crafting workshop starts, participants will need to complete an outcome measure to determine their degree of need crafting, current need satisfaction, and perceived need-support from their immediate managers. The three measuring instruments to be used for the effect evaluation are discussed below (De Angelis et al., 2020). These instruments were selected for their direct alignment with the constructs in the intervention’s program theory and their operationalization, as well as for their explicit grounding in SDT. The adapted NCS operationalizes the proximal outcome targeted by NC (need crafting) and has been validated in the South African work context (Putter et al., 2024). The TMIB-S operationalizes the proximal outcome targeted by NN (perceived need-supportive managerial behaviors) and was developed and validated from an SDT perspective (Huyghebaert-Zouaghi et al., 2023). The single-item need satisfaction scales capture the distal outcome (basic psychological need satisfaction) while minimizing respondent burden across repeated measurement waves, with validity and reliability comparable to multi-item scales (Martela and Ryan, 2026).

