The first instrument will be an adapted version of the Need Crafting Scale (NCS) (Laporte et al., 2021), comprising nine items. The original scale was adapted by Putter et al. (2024) to better suit the work context by making small changes to the instructions as well as the wording of items (i.e., references to “in their lives” were changed to “at work,” and “people” were replaced with “colleagues”). Only the three action-oriented items of each subscale will be administered, while the negatively phrased items will be omitted. Previous research found no significant value added from the negatively phrased items, as these items did not load significantly onto their *a priori* factors when controlling for the method factor (Putter et al., 2024). These nine items will be rated on a five-point Likert scale, ranging from 1 (completely not true/disagree) to 5 (completely true/agree). Examples of the items include “*I deliberately choose activities I am good at*” (competence crafting action), “*As much as possible, I try to do things that I really want to do rather than things that have to be done*” (autonomy crafting action), and “*Even when I feel lonely, I still try to contact colleagues who care for me*” (relatedness crafting action).

The second instrument will be the Tripartite Measure of Interpersonal Behaviors-Supervisor (TMIB-S), comprising 22 items, which will measure need-oriented leader behaviors (Huyghebaert-Zouaghi et al., 2023). However, only the “need-supportive behaviors” subscale that comprises eight items will be used to determine the degree to which managers are perceived as supportive following the intervention. Examples of items include “*My supervisor shows that they understand my perspective*” (autonomy support), “*My supervisor recognizes my efforts and accomplishments*” (competence support), and “*My supervisor shows care and concern*” (relatedness support). The need-supportive behaviors subscale will be answered through a seven-point Likert scale, ranging from 1 (strongly disagree) to 7 (strongly agree) (Huyghebaert-Zouaghi et al., 2023). These three instruments will be administered at T2 to T4 (Groups 1 and 2) and T4 to T6 (Group 3).

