##### Before the intervention

2.9.1.1

As part of the onboarding process – to prepare employee and managerial participants for the intervention and determine their readiness for such a study – the first process measurement will be administered. This process measurement will capture elements central to participants’ buy-in (i.e., participants’ readiness for change and communication). These and subsequent process measures will be drawn from the Intervention and Multiphase Training Transfer Assessment Questionnaire (IMTTAQ; Vasquez et al., 2026), a validated instrument that assesses contextual factors, transfer mechanisms, and behavioral outcomes across the pre-training, during-training, and post-training integration phases of occupational health training interventions. Examples of the items are “*I am ready to accept the changes brought about by the intervention*” [readiness for change; four items, adapted from Randall et al. (2009)] and “*I have received information about the goals of the intervention*” (communication; three items). These will be measured on a five-point Likert scale, ranging from 1 (strongly disagree) to 5 (strongly agree).

It will, furthermore, also be important to determine participants’ degree of job resources (i.e., autonomy) and job demands (i.e., workload). Example items are “*I am given a lot of freedom to decide how to do my own work*” and “*I never seem to have enough time to get everything done in my job*” [NIOSH Worker Well-Being Questionnaire (WellBQ)] (Chari et al., 2024). These two items will be measured on a four-point Likert scale, ranging from 1 (strongly disagree) to 4 (strongly agree). These two, as well as the above seven items, will be collected at T1 (Groups 1, 2, and 3) and again at T3 (Group 3) (see Figure 1).

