Fifth, all outcome and process measures are self-reported, raising concerns about common method bias and socially desirable responding (Podsakoff et al., 2024); temporal separation of measurements and guaranteed anonymity should attenuate, but cannot eliminate, these risks. Self-report nonetheless remains the theoretically appropriate source for the focal constructs: need satisfaction is an internal experience, and need-supportive leadership is theorized to operate through employees’ perceptions of support. Objective indicators (e.g., absenteeism or turnover records) lie further downstream and depend on organizational record release and are therefore reserved for future research. Sixth, the follow-up period extends only to 1 month after training, which limits conclusions about the sustainability of intervention effects. This horizon reflects the terms of the research agreement with the host organization and the need to limit attrition and organizational-change confounds across an already intensive six-wave measurement design; proximal behavioral outcomes are expected to change within weeks, whereas longer-term sustainability is explicitly positioned as a direction for future research. Seventh, although validated and pragmatic for repeated administration, the single-item need satisfaction measures (Martela and Ryan, 2026) limit the modeling of measurement error and of subdimensions of need satisfaction. Finally, the intervention targets only the individual and leader levels of the IGLO framework (Nielsen et al., 2017); group- and organizational-level factors are measured as context but not intervened upon, and the facilitator’s dual role as researcher may introduce demand characteristics.

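### Departments are allocated before the T1 pre-test with no step that withholds the result, so the self-reported baseline of the only randomized comparison (Group 1 versus Group 3) is open to knowledge of allocation

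*Protocol article*

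**What the plan says.** Section 2.7 (Data collection and timeline) lists the stages in order: "allocate departments to three groups; perform the pre-test data collection on all three groups at the same time and under the same conditions (T1"), followed by training of Groups 1 and 2. Section 2.5 (Allocation to intervention) treats the departments that sign up as clusters, "followed by randomization (e.g., using a random number generator) to assign each department to either Group 1 (immediate intervention) or Group 3 (delayed intervention"). Its next sentence reads: "Participants without participating managers will automatically be assigned to Group 2". Section 2.1 (Study design) uses a different unit: "departments whose managers do not volunteer will form Group 2 (NC only, non-randomized"). Section 3.1 (Limitations) also describes Group 2 as made up of departments.

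Section 3.1 states that "all outcome and process measures are self-reported". No section describes concealment of the allocation or says when participants learn their group.

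The article is not consistent about what T1 contains. Section 2.7 describes a pre-test common to all groups and a repeat of that same battery for Group 3 at T3. Section 2.8.1 (Outcome measures) instead says "On the day of training, but before the need crafting workshop starts, participants will need to complete an outcome measure", and then "These three instruments will be administered at T2 to T4 (Groups 1 and 2) and T4 to T6 (Group 3"). Section 2.9.1.1 (Before the intervention) places nine readiness, communication, autonomy and workload items at T1; these "will be collected at T1 (Groups 1, 2, and 3) and again at T3 (Group 3").

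**The concern.** A baseline is a safe reference only if it cannot depend on the allocation. Here the departments are already in their groups when T1 is answered, and the answers are subjective ratings of one's own crafting, one's manager and one's needs, or of readiness for the intervention. Employees who know that they will wait, or that their manager is about to be trained, may answer differently for that reason alone. Section 3 (Discussion) itself accepts that delayed access may reduce motivation. Section 3.1 notes that the facilitator is also the researcher, and nobody independent is described as holding the allocation.

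Group 1 versus Group 3 is the only comparison that randomization supports. If its baseline can be affected by knowledge of the group, part of that protection is lost, and this cannot be repaired once T1 has been collected. A second, smaller risk is that simple randomization of a modest number of departments could leave the two arms clearly unequal.

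**Working it through.** **1. Order.** Section 2.7 places allocation before T1. Section 3.1 makes all measures self-reports. Nothing between the two steps withholds the result. The exposure follows from these three facts and holds on each reading of the timeline:

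- If T1 includes the outcome instruments (section 2.7), the outcome baseline is taken after allocation.
- If T1 holds only the nine items of section 2.9.1.1, those items include readiness to accept the intervention's changes. That is sensitive to knowing one's group, and sections 2.10.2 and 2.10.3 use readiness as a context moderator.
- If the outcome baseline is taken on training day (section 2.8.1: T2 for Groups 1 and 2, T4 for Group 3), Group 1 answers knowing that it is about to be trained, and the two randomized groups have no common outcome baseline.

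**2. Effect on the estimate.** Section 2.8.2 plans time-by-group interactions. For Group 1 versus Group 3 before Group 3 is trained, the contrast is

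(post₁ − pre₁) − (post₃ − pre₃).

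If knowledge of the group shifts pre₃ by δ and nothing else, the contrast moves by +δ. If it shifts pre₁ by δ, the contrast moves by −δ. The whole shift enters the estimate. The article gives nothing from which δ could be sized.

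**3. Imbalance, if the generator means simple 1:1 randomization.** The article gives no figure to reproduce and no number of departments, so K is an assumption and a range is shown. With X ~ Binomial(K, 0.5) departments in Group 1, *2:1 or worse* means that the larger arm has at least twice as many departments as the smaller.

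| K (assumed) | P(equal split) | P(2:1 or worse) | P(one arm empty) |
|---|---|---|---|
| 4 | 0.375 | 0.625 | 0.125 |
| 6 | 0.312 | 0.688 | 0.031 |
| 8 | 0.273 | 0.289 | 0.008 |
| 10 | 0.246 | 0.344 | 0.002 |
| 12 | 0.226 | 0.388 | 0.0005 |
| 16 | 0.196 | 0.210 | below 0.0001 |
| 20 | 0.176 | 0.115 | below 0.0001 |

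Example, K = 8: 2 × (1 + 8 + 28)/256 = 74/256 = 0.289. The column is not monotone because the possible splits are discrete; with K = 6, every unequal split is 2:1 or worse.

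**4. Cost of an unequal split.** The between-department variance of the contrast is proportional to 1/a + 1/b for a and b departments per arm. For K = 8, relative to 4:4:

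- 5:3 gives (1/5 + 1/3)/(1/4 + 1/4) = 1.07.
- 6:2 gives (1/6 + 1/2)/(1/4 + 1/4) = 1.33.

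**5. Equal numbers alone do not balance department characteristics.** With K/2 departments per arm, the chance difference in a department-level covariate has SD √(4/K), in units of the covariate's SD. By the normal approximation, the probability of a difference above 0.5 SD is 0.62 (K = 4), 0.48 (K = 8), 0.39 (K = 12) and 0.26 (K = 20). This is the case for restricting on a covariate as well as on number.

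**The case against.** The strongest reply is that much of the risk is inferred, and several parts of that reply stand.

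- **Disclosure.** A reader might infer that employees are told their group before T1. The article does not say so; allocating is not announcing, and section 2.7 asks for the same conditions in all groups. Disclosure is not excluded, and that is as far as the text goes.
- **Unrestricted randomization among a few unequal departments.** A reader might infer this too. Section 2.5 names the generator only as an example and is silent on blocking or stratification, which an article may leave to the full protocol. The number and sizes of departments are not given. At K = 8, a 4:4 or 5:3 split occurs with probability 182/256 = 0.71, and 5:3 costs only about 7% in between-department variance.
- **Movement into Group 2 after randomization.** The sentence in section 2.5 could be read as taking people out of their randomized group. Read with section 2.1, it can equally describe a rule applied at sign-up. What stands is a mismatch of unit, participants against departments, with no timing given.
- **Reach of the fix.** H1 to H3 concern Groups 1 and 2, and none names Group 3. Group 2 is fixed by manager non-participation, a self-selection that section 3.1 acknowledges, so re-ordering cannot protect those contrasts.

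The reply does not remove the stated order. Allocation before a self-reported baseline is written into section 2.7, so it is a choice in the plan and not a detail left to another document.

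**Conclusion.** The point holds in a limited form. The plan allocates before T1, relies wholly on self-report and includes no step that withholds allocation, so the baseline of Group 1 versus Group 3 is open to knowledge of the group. This is an exposure, not a demonstrated bias, and its size cannot be derived from the article.

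The imbalance risk is secondary and conditional. If the generator means simple randomization, the probability of a 2:1 or worse split is about 0.12 to 0.69 over an assumed 4 to 20 departments, and it is smallest at the top of that range.

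The document does not support saying that randomization is unrestricted, that participants are told their group before T1, or that people will leave their randomized group. The change is still worth making because it is nearly free and cannot be made after T1.

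**What to change.** Rewrite sections 2.5 and 2.7 so that the steps run in this order:

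1. At sign-up, record each manager's decision and form Group 2 by whole department. Use the same unit in sections 2.1, 2.5 and 3.1.
2. Collect T1 from everyone.
3. Randomize the remaining departments in equal numbers to Group 1 or Group 3, restricted on department size. For an even number of departments, this sets the probability of an unequal split to zero.
4. Announce the groups only after that.
5. Analyse each department in the group to which it was randomized, including where a manager later withdraws.

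Reconcile section 2.7 with section 2.8.1 on whether the outcome instruments are given at T1. Only if they are can the allocation also be restricted on T1 leader support, and only then does the re-ordering protect the outcome baseline. Otherwise it protects the T1 process and context items alone.

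The cost is a re-ordering of existing steps and a short allocation procedure, with no added participants or measures. The downside is that groups are announced later. The change does not help the contrasts with Group 2, and the text should say so.
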